#### 6.4 Safety concerns related to study procedures

**EGG with non-caloric and caloric satiety testing:** Due to the presence of diabetic gastroparesis, meal boluses for the control of postprandial hyperglycemia will be started when the REAL-time CGM confirms that glucose concentrations start to rise after Ensure® ingestion. This approach is aimed at minimizing incorrect insulin bolus administration and nutrient due to delayed and possibly erratic gastric emptying. EGG recording involves placement of EGG electrodes on the abdominal skin. There may be some soreness in removing the EGG electrodes.

**Other Risks:** Blood draw may cause discomfort, such as swelling, temporary sensation of pain, burning, or a bruise that may develop and last for a few days. Less common risks include a blood clot at the site of puncture, swelling of the vein and surrounding tissues, and possible bleeding from the puncture site.

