### 2.2 Diabetic gastroparesis

It is well established in the literature that optimal control of blood sugar in patients with long-standing diabetes mellitus slows the progression of several of the systemic complications of the disease, including peripheral neuropathy and renal disease. Gastrointestinal manifestations are prevalent in individuals with diabetes, especially in those who have had poorly controlled disease for 10 or more years. Nausea, vomiting, fullness, early satiety, bloating, discomfort, and altered glycemic control represent the symptoms of diabetic gastropathy. Many individuals with diabetic gastropathy exhibit delays in gastric emptying of solid meals and are considered to have gastroparesis. However, studies of the effects of hyperglycemia on gut function have been limited to acute settings in which some parameter of muscular, myoelectrical, or sensory function is modulated by acute experimental changes in blood glucose.

In diabetics, induction of hyperglycemia slows both solid and liquid phase gastric emptying, blunts phasic antral contractions, and leads to generation of gastric slow wave dysrhythmias such as tachygastria. In healthy non-diabetic volunteers, acute hyperglycemia also induces tachygastria and blunts antral contractility. Acute hyperglycemia also increases gastric sensitivity to mechanical stimulation, and reduces responses to prokinetic drugs. On the basis of these acute studies, gastroenterologists routinely recommend optimal glycemic control to minimize gastrointestinal consequences of poorly controlled diabetes. However to date, there remains no hard data from well-controlled, long-term trials to validate this recommendation.

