### 5.1 Visit schedule overview

The patient-related activities of the GLUMIT-DG study can be divided into 3 phases:

- **Screening Phase:** Screening to determine eligibility and receive training on the use of an iPro which is a CGM used for retrospective analysis of CGM results. While wearing the device the subject is blinded to their sensor glucose values. This period is so that the subjects can demonstrate a willingness to wear a sensor, gain proficiency in inserting a sensor, and provide the study baseline data of their CGM readings (retrospectively). This will occur over 2-8 weeks and include 2 visits for gastric related testing as well as iPro training. To progress in the study the subject will need to have at least 216 hours of iPro readings.
- **Run-in Phase:** Initiation of insulin pump training and training in the use of real-time CGM (4 visits over a minimum of 2 weeks up to a maximum of 8 weeks)
- **Follow-up Phase:** Study treatment to assess the safety of using RT-CGM as an adjunct to SMBG-guided insulin pump therapy over 24 weeks (6 visits)

The visit and data collection schedule described below in detail is summarized in Appendix 10.2

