### 5.3 Screening visits and iPro training

**Screening visit 1:** The patient should be in a fasting state (no food or drink except up to 120 mL (4 oz) of water after midnight the night before) for this visit. The patient will sign the GLUMIT-DG consent at or prior to screening visit 1 and will undergo a history and physical examination to identify other illness and contraindications for participation. In addition, blood will be drawn to measure their hemoglobin A1c level. A patient's hemoglobin A1c level must be 8.0% or higher in order to be eligible for this study. Laboratory test results that need to be recorded from chart review or obtained as part of screening include: complete blood count (CBC): white blood cells, red blood cells, hemoglobin, and platelets; a comprehensive metabolic panel: sodium, potassium, chloride, carbon dioxide, calcium, glucose, blood urea nitrogen (BUN), creatinine, albumin, total protein, alanine aminotransferase (ALT), aspartate aminotransferase (AST), and bilirubin; and thyroid stimulating hormone (TSH). The Patient Assessment of Upper Gastrointestinal Disorders - Quality of Life (PAGI-QOL) and the Patient Assessment of Upper Gastrointestinal Disorders - Symptom Severity Index (PAGI-SYM) questionnaires will also be completed as well as the Baseline Medical History and Physical Examination forms.

**iPro training:** At a clinic visit as early as possible during the screening phase, patients will be seen by a diabetes educator to undergo training on measuring their interstitial glucose levels using the iPro. The iPro involves wearing a sensor device, which has a needle that is inserted in the subcutaneous tissue to continuously measure blood glucose levels. The sensor is calibrated according to blood glucose results taken from finger sticks. This is a device that collects interstitial glucose readings, but the readings are not displayed to the patient, so no insulin dose decisions are made based on CGM readings. Patients will measure their blood glucose levels using a standard finger stick method and will be required to do so 4 times daily using a glucose meter. During this period, patients will continue to take their regular diabetes medications or insulin treatment including those who already wear an insulin pump. This iPro data will not be used for adjustment of diabetes therapy since the patient cannot see the data.

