**Screening visit 2:** Patients should consult with their GLUMIT-DG certified endocrinologist 24 hours prior to visit and return to the clinical center in a fasting state (no food or drink except up to 120 mL (4 oz) of water after midnight the night before) on a separate day after the first screening visit to continue with study procedures and baseline data collection for electrogastrograms with non-caloric and caloric satiety tests (EGG), electrocardiogram (ECG), and autonomic function testing. If patients normally take insulin, they will be asked to take only their normal BASAL insulin and hold meal insulin, using supplements of insulin to correct high glucose AS PER their doctor's instructions. If patients are using a pump, they will be requested to keep their usual basal rate and hold meal boluses and to use supplemental insulin if their home glucose meter indicates a high glucose by using the bolus calculator of their insulin infusion pump or as suggested by their doctor's instructions. Upon arrival to the clinic, patients will have

10 mL of blood drawn for plasma banking to measure inflammatory and immune markers or plasma proteins to ascertain the effects of controlling blood glucose during the GLUMIT-DG study. Patients will have their blood glucose level measured using a finger stick method to ensure their blood glucose is less than 270 mg/dL. If the blood glucose level is higher, then a blood sample will be taken and sent to the lab for confirmation and supplemental insulin will be ordered by the endocrinologist or diabetes educator of the research team to decrease the blood glucose to less than 270 mg/dl. Once confirmation is made that the patient's blood glucose level is less than 270 mg/dL, the electrogastrograms with non-caloric and caloric satiety tests will be performed.

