patients will drink a cup (150 mL) of refrigerated (at 4 degrees C) Ensure® (1.1 kcal/mL) at a rate of 150 mL every 5 minutes until they feel completely full. Patients will drink from an opaque cup which will be filled out of sight so that the volume consumed is not readily apparent to minimize the potential of introducing an assessment bias. In addition, no information regarding the total volume of Ensure® ingested will be communicated to the patient. The total volume of Ensure® ingested will be recorded on the EGG and Satiety Test form. The satiety test will be analyzed by the total amount of Ensure® consumed. Symptoms of nausea, bloating, abdominal discomfort, hunger, and stomach fullness will be recorded on a visual analog scale at baseline and at 10, 20, 30, and 60 minutes after ingestion of Ensure®. The electrodes will then be removed. The EGG will be analyzed for the fasting and post nutrient load periods corresponding to symptom assessments at 0-10, 11-20, 21-30, 31-40, 41-50 and 51-60 minute intervals. The percentage distribution of the power in the normal frequency range (2.5-3.75 cycles per minute [cpm]), tachygastria (>3.75-10 cpm), bradygastria (<2.5 cpm) and duodenal-respiration (>10 cpm) will be calculated. A power ratio comparing mean signal amplitudes between postprandial and preprandial power will be calculated. The dominant frequency, and the percentage of time in the dominant frequency will be calculated and recorded.

Patients will receive 1 unit of insulin for every 15 grams of Ensure® consumed during the caloric satiety testing to reduce the likelihood of severe postprandial hyperglycemia. Patients blood glucose levels will be closely monitored using their home glucose meter. Patients will be monitored for 2 hours after beginning the Ensure® satiety testing to assure their blood glucose level does not exceed 300 mg/dL. If a patient's blood glucose level exceeds 300 mg/dL, additional insulin will be given to bring it down to 250 mg/dL as per the suggestion of the endocrinologist or diabetes educator of the team.

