#### 5.4 Run-in visits with insulin pump training

After successful completion of iPro (or iPro2) training, patients will return for four weekly visits, for a minimum of two weeks up to an 8-week learning period to receive training on the usage of an insulin pump coupled with RT-CGM. Participants will be trained on how to use a computer to send the data gathered by the RT-CGM, glucose meter and insulin pump to their study physician and diabetes educator. During the run-in period insulin pump infusion parameters will be adjusted to optimize regulation of blood glucose levels, using information from both their SMBG and from trend analysis of the RT-CGM which will be used only as an adjunct to SMBG.

**Run-in visit 1:** Participants will receive instruction on use of the RT-CGM, including the uploading of the data using the CareLink system as well as instructions on glycemia management using their SMBG which will be supplemented with the trend identification using the RT-CGM. The RT-CGM has a feature known as “REAL-Time Alarms” which will be set to warn patients when their glucose levels are very low or very high. The hypoglycemic alarm threshold will be set at 80 mg/dL and the hyperglycemic alarm threshold will be set at 240 mg/dL. The low glucose snooze will be set between 15-20 minutes to allow time to observe the effect of treatment for the hypoglycemia, and the high glucose snooze will be set to 1-2 hours to allow time to observe the effects of a corrective dose of insulin. They will be taught how to calibrate their RT-CGM using 2-4 glucose readings each day, obtained when there is a low rate of glucose change, as indicated by an absence of rate of change arrows. The subjects will be instructed to not make any insulin dose decisions based on the RT-CGM glucose reading without obtaining a blood glucose measurement using their glucose meter. Insulin doses may be modified based on the glucose rate of change, as was done during the JDRF and STAR 1 and STAR 3 trials. (See package insert for instructions for use of CGM)

**Run-in visit 2:** This visit should be planned within a week after the first run-in visit. Patients will be taught insulin infusion pump mechanics and will be started on an insulin pump filled with saline. The purpose of filling the pump with saline is to ensure that the patient can tolerate wearing it before it is filled with insulin.

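### Section 6.4 ties the start of satiety-test insulin to a real-time CGM signal that cannot be read at the baseline test, so insulin timing around the post-Ensure EGG can differ between baseline and follow-up.

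*Protocol*

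**What the plan says.** Section 6.4, in its paragraph on the EGG with satiety testing, says that meal boluses "will be started when the REAL-time CGM confirms that glucose concentrations start to rise after Ensure® ingestion". It does not limit this to any visit.

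The procedure text is different in kind. Section 5.3 states for the baseline test: "Patients will receive 1 unit of insulin for every 15 grams of Ensure® consumed during the caloric satiety testing". Section 5.6 repeats this amount rule at weeks 12 and 24. None of the three places says when the insulin starts or mentions a CGM trigger.

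On the devices, Section 5.1 says of the iPro used in screening: "While wearing the device the subject is blinded to their sensor glucose values". Section 5.3 adds that "the readings are not displayed to the patient, so no insulin dose decisions are made based on CGM readings". The same section places the "electrogastrograms with non-caloric and caloric satiety tests (EGG), electrocardiogram (ECG), and autonomic function testing" at screening visit 2. RT-CGM first appears at run-in visit 1 in Section 5.4: "Participants will receive instruction on use of the RT-CGM".

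Three further places bear on CGM-guided insulin. Section 5.4 instructs subjects to "not make any insulin dose decisions based on the RT-CGM glucose reading without obtaining a blood glucose measurement using their glucose meter". Section 5.5 likewise makes the meter result the basis of every insulin decision. Section 5.7 (Meal Boluses) allows the bolus to be held back until RT-CGM shows a rise, but only as an option in some patients.

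**The concern.** A rule written for a repeated test should be workable each time the test is done. This one depends on a device that the patient does not yet have at baseline. If sites follow Section 6.4 where they can, at weeks 12 and 24, and do something else at screening, the test conditions change at the same point as the treatment.

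That matters because the protocol itself links glucose to the quantity measured. Section 2.2 says that inducing hyperglycemia in diabetics "leads to generation of gastric slow wave dysrhythmias such as tachygastria". The percentages of tachygastria, bradygastria and normal 3 cpm activity at baseline, 12 and 24 weeks are a secondary outcome (Design synopsis; Section 8.2), and fewer slow-wave rhythm disturbances is one of the secondary hypotheses (Section 8.1). The trial has no control group, so no concurrent arm would reveal a shift due to test conditions. If the seven centers settle the ambiguity differently, variation between sites is added as well.

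**Working it through.** No formula applies and the plan gives no figure to reproduce. The check sets the texts side by side.

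| | Screening visit 2 | Week 12 | Week 24 |
|---|---|---|---|
| CGM worn | iPro, retrospective, hidden from patient (5.1, 5.3) | RT-CGM (5.6) | RT-CGM (5.6) |
| Glucose followed during the test by | home meter (5.3) | meter, with RT-CGM as supplement (5.6) | meter, with RT-CGM as supplement (5.6) |
| Insulin amount | by Ensure consumed (5.3) | same (5.6) | same (5.6) |
| Start time in the procedure text | none | none | none |
| Section 6.4 trigger readable | no | yes | yes |

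1. *Can the trigger be read at baseline?* No. Appendix 11.2 agrees with the visit text: the satiety test is marked under screening and not run-in, and RT-CGM training under run-in and not screening. Section 5.3 does have staff review CGM data before the test, but that is a check of past readings, not a live signal during it.
2. *Does the procedure text supply a common timing?* No. The amount rule is the same at all three visits, but the start is unstated at each of them.
3. *Does Section 6.4 fit the other rules on CGM-guided insulin?* Not fully. Section 5.7 leaves the delay optional for some patients, whereas Section 6.4 states it as what will happen in this test. Sections 5.4 and 5.5 call for a meter value, and Section 6.4 mentions none.
4. *Which recordings are exposed?* Only the 60-minute EGG after Ensure. No insulin is tied to the water-load test, and the 15-minute fasting recording comes before the Ensure.

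So the trigger is available at two of the three tests and missing at the one that serves as the reference for change.

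**The case against.** The strongest reply is that Section 6.4 and the procedure text do not contradict each other at follow-up: one gives the start, the other the amount, and they can be read together. That is right for weeks 12 and 24. It does not help at baseline, where the start rule cannot be carried out and nothing replaces it.

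A reader might infer that baseline and follow-up EGGs definitely are recorded under different insulin timing. The protocol does not support that. Baseline timing is not stated, and a site that works from Sections 5.3 and 5.6 alone could treat all three visits alike. A difference is possible, not established.

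A reader might also see a flat conflict with the rule against acting on RT-CGM alone. That goes too far. Section 5.4 permits insulin doses to be modified on the glucose rate of change, Section 5.7 foresees a CGM-guided delay, and meter values are available during the follow-up tests. What remains is that Section 6.4 omits the meter value.

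Other differences between visits are real: glucose immediately before the test may lie anywhere from 100 to 270 mg/dL, and background therapy changes to the pump. Section 8.3 concedes that evidence of efficacy needs a larger controlled study. These points limit what the comparison can show, but they do not excuse a further difference that wording can avoid. The two hours of monitoring with a 300 mg/dL action level is a safeguard; it does not standardise timing.

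**Conclusion.** The point stands as an internal inconsistency with a possible effect on one comparison. A rule stated without limit to any visit cannot operate at the baseline test, and the remaining text does not say when insulin starts. The before/after comparison of the post-Ensure rhythm measures, which is part of one secondary outcome, may therefore mix the effect of treatment with a change in test conditions.

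The size and direction of any such effect cannot be derived. The post-Ensure recording is analysed in six 10-minute intervals, so each interval is 1/6, or about 17%, of it. A reader might be tempted to count the intervals that fall within a supposed insulin delay and call that the bias. It would not be one: the protocol does not say how long a delay would be, or how far it would move glucose or rhythm within the hour.

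The conclusion assumes that sites apply Section 6.4 at follow-up, where it is workable, and that the baseline test is done in screening on the iPro, as scheduled. The water-load EGG, the primary hypoglycemia outcome and the sample size are not affected.

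**What to change.** Reconcile Section 6.4 with the caloric test text in Sections 5.3 and 5.6 and with Sections 5.4, 5.5 and 5.7. The result should be one insulin-timing instruction for the caloric satiety test that can be carried out in the same way at screening visit 2, week 12 and week 24. Which rule that is, and how it relates to the meter requirement, is for the study clinicians. The statistical need is only that it be the same at all three visits.

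Add fields to the EGG form for the time insulin was given and for the glucose values already monitored during the test, so that comparability can be checked. No extra glucose measurements are needed.

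The cost is a small change of wording and form. The one real constraint is that a trigger available only at follow-up could not serve as the common rule.

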#### 6.5 Safety issues related to patient privacy

It is the investigator's responsibility to conduct the protocol under the current version of Declaration of Helsinki, Good Clinical Practice, and rules of local IRBs. The investigator must ensure that the patient's anonymity is maintained in their data submission to the Data Coordinating Center. Patients will be identified only by an identification code but not by their name, SSN, or hospital medical record number. Investigators will maintain a separate confidential enrollment log which matches identifying codes with the patients' names and addresses (i.e., available only to local clinic staff). All study material will be maintained in strict confidence.

#### 6.6 Adherence and retention

Two important goals of the GLUMIT-DG study are to optimize adherence to the glycemic control regimen through use of the RT-CGM coupled with the insulin pump and to maximize the retention of participants in the study. Assessment of adherence to usage of the RT-CGM and insulin pump during the run-in period will provide clinic staff a means to identify participants having problems with adherence. Adherence will be assessed by:

- Patients displaying the ability to conduct blood glucose monitoring using a standard finger stick method at least 4 times daily
- Patients displaying the ability to successfully wear and manage the RT-CGM along with the insulin infusion pump evidenced by RT-CGM usage results
- Patients displaying the ability to electronically transfer RT-CGM data and insulin infusion pump data to a computer for submission to the study staff

These assessments will guide the consideration of strategies to improve adherence.

#### 6.7 Management of diabetes

All other illnesses will be managed in conjunction with the patient's primary care physician. Diabetes care will be provided per GLUMIT-DG protocol (see Section 5.5 Follow-up visits and insulin dose adjustments). Treatment approaches for gastroparesis and nutritional counsel are described in the

Standard of Care for Patients with Diabetic Gastroparesis (SOP IV) document prepared by the GpCRC Steering Committee.

---

## 7. Adverse Event Monitoring

---

The GLUMIT-DG study will monitor and report adverse events to ensure patient safety according to local IRB guidelines and the “Common Rule”, which is a government regulation that requires written procedures and policies for ensuring reporting of “unanticipated problems” involving risks to study participants. The FDA Guidance for Clinical Investigators on Adverse Event Reporting to IRBs - Improving Human Subject Protection document also provides recommendations for adverse event reporting, while specifically focusing on unanticipated event reporting. The FDA recommends that careful review of whether an adverse event is an unanticipated event that must be reported to IRBs should be considered while adhering to local IRB guidelines.

### 7.1 Definitions

**Adverse event:** An adverse event is any untoward medical occurrence that may present itself during a research study which may or may not have a causal relationship with the treatment or study participation. Adverse events include any unanticipated problems involving risks to participants, or breaches of protocol which might entail risk to participants. The term “unanticipated problem” includes both new risks and increased occurrence of anticipated problems.

**Severe hypoglycemic events** occur when a patient’s capillary glucose falls below 50 mg/dL and the patient is incapable of self treatment, hence needing the assistance of a third party (friend, relative, paramedic, etc) for resolution of the hypoglycemia. This type of event will be recorded on study form(s). If a patient has more than two severe hypoglycemic events (i.e., ER visit, relative, etc.) during the study, he/she will be re-evaluated with the diabetologist with an option to be placed back on the previous diabetes medications or insulin regimen. Study staff will follow up with patients to ensure that severe hypoglycemic events were properly managed and make any necessary modifications to their treatment.

**Severe hyperglycemic events** occur when a patient’s capillary glucose is above 500 mg/dL as revealed on an finger stick reading (SMBG, confirmed by a reference glucose value if available) and/or a blood ketone test of 0.6 mmol/L or higher and/or the presence of nausea, vomiting or altered mental status. The patient may be symptomatic (polyuria, polydipsia) or with concurrent illness, but capable of good communication or the patient’s symptoms may be intense, or the patient is incapable of good communication and immediate transport to emergency department may be necessary. These severe hyperglycemic events will be recorded on study case report forms according the procedures for SAEs in Section 7.3.

**Serious adverse event:** A serious adverse event (SAE) is an adverse event occurring at any time during the study that results in death, life-threatening adverse experience, inpatient hospitalization or prolongation of existing hospitalization, a persistent or significant disability or incapacity, or a congenital anomaly or birth defect. Severe hypoglycemic and severe hyperglycemic events will be considered an SAE. Other events may also be considered an SAE if, based on medical judgment, the event jeopardized the patient to the point of requiring medical or surgical intervention to prevent the occurrence of any of the conditions for an SAE listed above.

**Sentinel events** are defined as the subset of serious adverse events involving severe hypoglycemic (<50 mg/dL) or hyperglycemic (>500 mg/dL) occurrences AND any of the following: loss of consciousness, seizures, hospitalization, emergency room visit, professional intervention, or death.

